#### Data analysis

General analytical strategy: as opposed to conventional superiority trials, in non-inferiority trials per-protocol analysis is generally preferable to intention-to-treat (ITT) analysis, because the postulated hypothesis being tested assumes no difference between the two interventions [68]. Indeed, in non-inferiority trials, a “conservative” approach relies on a per-protocol analysis, which maximizes the probability of finding a statistically significant difference between the two groups, i.e. of rejecting the hypothesis that has motivated the trial. Moreover, the ITT approach includes all individuals who were initially randomized, regardless of their adherence, and thus may dilute, or even mask, the true difference between the interventions in the case of non-adherence or losses to follow-up [59]. In the extreme, if most participants do not adhere to the assigned intervention or fail to complete the follow-up assessment, the ITT analysis will automatically show no difference. To prevent such paradoxes, our main analysis will rely on the per-protocol approach, i.e. include only participants who will have completed the one-year assessment. On the other hand, because of its popularity, we will use the ITT approach in “sensitivity analyses,” as recommended by the CONSORT guidelines for non-inferiority trials [68]. Furthermore, our analyses will focus on (primary or secondary) outcomes at one year. Because all primary and secondary outcomes are measured on continuous scales, the methods outlined below for the analyses of the primary outcome will also apply to all secondary outcomes. However, the analysis of secondary outcomes will be exploratory in nature and some (e.g. for PFM function) may have more limited statistical power.

Preliminary descriptive analyses will compare the individuals in the two trial arms using means, medians, standard deviations, and interquartile ranges (IQR) for continuous variables and frequency distributions for categorical and binary variables. Any variable for which the difference between the two arms is considered clinically relevant will be adjusted for in the multivariable regression analyses (see below). The distribution of the outcome scores will be assessed for normality of residuals, using the Shapiro–Wilk test. In the case of significant violation of normality, appropriate parametric (e.g. logarithmic or Box-Cox) [77] or non-parametric [78] transformation will be applied, to meet the normality assumption underlying the univariate t-tests, as well as multivariable linear regression (see below).

Analyses for the primary outcome at one year (and secondary outcomes): The primary analysis will test our main hypothesis that group-based classes are not inferior to individualized treatment with respect to the primary outcome of relative (%) reduction in the number of leakages at one year post randomization. (For all outcomes, the analyses outlined below will be repeated using data on post-intervention assessment.) As recommended for non-inferiority trials, the hypothesis of non-inferiority will be accepted if, and only if, the upper bound of the two-tailed (1-2α) 95% CI (corresponding to a conservative Type I error of 0.025 for the one-tailed independent-group t-test) for the mean difference (in % reduction) excludes the non-inferiority threshold [68], set at 10% difference. This basic analysis will be extended to multivariable analyses. Specifically, two multivariable linear models, of increasing complexity, will be used to adjust the estimated difference between the % reduction at one year in the two groups for, respectively, (1) only the two stratification variables (center and type of UI), as well as the baseline number of UI episodes (to account for regression to the mean phenomenon); and (2) (if necessary) in addition to variables in model (1): any variable, for which a clinically important imbalance between the two arms is revealed by descriptive analyses (see above). In both models, the two-way interactions between the trial arm and (a) center and (b) UI type, will be tested using 1-df model-based F-tests to verify if the difference between the effects of the two interventions depend on either of those stratification variables. In the case of a statistically significant interaction (*p* < 0.05 for the F-test), the intervention effects will be estimated and tested separately in the respective subgroups [79]. The results of multivariable linear regression analyses will be summarized in terms of adjusted mean difference between the outcomes in the two trial arms, together with the 95% model-based CIs. In sensitivity analyses for primary and secondary outcomes at one year, ITT analyses will be conducted, using the same statistical methods.

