### Interventions

The women in both groups receive the same 12-week PFMT, either in one-on-one sessions or as part of a group, under the direction of an experienced physiotherapist trained in pelvic floor rehabilitation. The choice of a 12-week PFMT approach is based on muscle physiology theory: strength-training programs show positive effect after 8–12 weeks [49]. In post-menopausal women, Gunnarsson et al. reported a significant improvement in strength and reduction in UI episodes after 12 weeks of training [50]. Both the one-on-one and group-based PFMT sessions are conducted once a week; participants are deemed to have successfully completed the program if they attended ten or more of the 12 sessions. Although there is no known side effect/complication related to PFMT other than possible discomfort following the intervention, any adverse event is monitored. All participants are instructed to contact research personnel should they experience any adverse event at any point during the study.

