#### Adherence

Based on the results of our previous feasibility study and post-study focus group, no significant problems are expected with treatment adherence in either group [22, 26]. Indeed, participants (*n* = 27) in the feasibility study complied well with study demands in terms of attendance at the treatment sessions (90%), completion of the daily exercise program (78%), and data collection (95%) [26]. Post-study focus groups identified “close supervision by the physiotherapist” and a “short daily PFM exercise program” as key facilitators in the participant’s completion of a 12-week group-based PFMT program and their adherence to the daily home PFM exercise program [22]. Adherence will be measured as follows: the women will be provided with diaries to record home exercise adherence for the 12-week treatment session. In addition, exercise maintenance will be assessed with a standardized questionnaire, at three and six months post intervention as well as at the 12-month follow-up evaluation. Additionally, adherence to each supervised weekly treatment sessions will be recorded by the physiotherapists.

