To ensure evaluation and treatment adherence, we used the following strategies: (1) individual consultations using vaginal digital palpation ensure that participants can perform a PFM contraction correctly (the physiotherapist is available before and after individual and group treatment sessions to provide tips and answer questions regarding the weekly treatment and home exercise program); (2) an exercise diary is given to each participant to bring home and is verified by the physiotherapist each week throughout the treatment; (3) the home exercise program comprises a short and simple daily PFM exercise program to facilitate exercise practice; (4) women in both groups are reminded of their appointments (evaluation and treatments) by a research assistant. They are scheduled at participants’ convenience; (5) follow-up contact calls are made at three and six months post intervention to maintain contact. Evaluators solicit information from participants on their intention to change address or telephone number and on the frequency of visits to incontinence-related medical professionals. They also verify if medications have been prescribed, surgery conducted, and if there are any other health problems likely to influence UI. Finally, they monitor their continued adherence to PFMT; and (6) participants are reimbursed for their travel and parking expenses related to participation in the study.

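### The per-protocol primary set has no adherence condition: it is a set of one-year completers and lacks the conservative property claimed for it

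*Protocol article*

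**What the plan says.** All of the following is in the Protocol article.

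- **Data analysis, reason for avoiding ITT.** The section says that "the ITT approach includes all individuals who were initially randomized, regardless of their adherence", and that it "may dilute, or even mask, the true difference between the interventions in the case of non-adherence or losses to follow-up". Per-protocol is presented as the conservative choice for a non-inferiority trial.
- **Data analysis, the set adopted.** "our main analysis will rely on the per-protocol approach, i.e. include only participants who will have completed the one-year assessment".
- **Interventions, the protocol's own completion criterion.** "participants are deemed to have successfully completed the program if they attended ten or more of the 12 sessions".
- **Adherence, data available.** "adherence to each supervised weekly treatment sessions will be recorded by the physiotherapists".
- **Data analysis, the secondary look.** At one year, "ITT analyses will be conducted, using the same statistical methods". Those methods are the independent-group t-test with its 95% confidence interval, and linear models for the percentage reduction.
- **Sample size calculation.** 155 evaluable women per arm (310 in total) and 364 recruited, allowing for 15% attrition. There is no allowance for excluding non-adherers.

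**The concern.** The definition does not follow from its justification. ITT is set aside because non-adherent women are counted in it, yet the set put in its place counts them too, provided they return at one year. A woman who attended none of the 12 sessions but completes the one-year assessment is in the per-protocol set. What separates this set from the randomized population is attendance at follow-up, not adherence to treatment.

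Two things are at stake. First, this set decides the trial's primary claim. If untreated or barely treated women are spread over both arms, they can pull the arm means together, and in a non-inferiority trial that favours the hoped-for conclusion. Second, selecting on the one-year assessment opens the analysis to attrition bias of unknown sign. Neither feature fits an analysis described as conservative.

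**Working it through.** **1. Reproduce the plan's figure.** Inputs from Sample size calculation: margin 10 points, SD 27, true difference 0, one-sided alpha 0.025, power 90%.

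- Normal approximation: n per arm = 2 × 27² × (1.960 + 1.282)² / 10² = 153.2, so 154.
- Non-central t: 155 per arm, power 0.902. This matches the stated 155.
- Attrition: 364 × 0.85 = 309.4, or about 310. Women expected to have no one-year outcome: 364 − 310 = 54.

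The 310 is simply the expected number of completers, so the sample size treats the primary set in the same way as Data analysis does.

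**2. What keeping non-adherers can do.** Assumptions, not in the documents: the deficit of group training (individual minus group) is exactly 10 points among adherers and zero among non-adherers, and a share s of non-adherers is present equally in both arms.

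- Difference in the analysed set = 10 × (1 − s).
- Distance to the margin = 10 × s.
- Standard error at 155 per arm = 27 × √(2/155) = 3.07.

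| s | Difference in set | Chance of declaring non-inferiority |
|---|---|---|
| 0% | 10 | 0.025 |
| 10% | 9 | 0.051 |
| 20% | 8 | 0.095 |
| 30% | 7 | 0.162 |

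The declaration is wrong with respect to adherers, the comparison that a per-protocol analysis is meant to address. The direction is not general: non-attendance concentrated in the group arm could widen the difference instead.

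**3. What excluding women without a one-year assessment can do.** If lost women improved D points less than completers in both arms, the completer difference falls short of the all-randomized difference by (loss in group − loss in individual) × D. Loss rates by arm and D are assumed.

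- Loss 20% group, 10% individual, D = 30 to 50: 0.10 × 30 = 3 and 0.10 × 50 = 5 points towards non-inferiority.
- The reverse split: 3 to 5 points against non-inferiority.
- Equal loss and equal D: zero.

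**4. What an adherence condition would cost in power.** The Adherence section reports 90% session attendance in a feasibility study of 27 women. Treating the 12 sessions as independent (an assumption), the chance of attending at least ten is 0.230 + 0.377 + 0.282 = 0.889.

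- 364 × 0.85 × 0.889 = 275 women, about 137.5 per arm: power 0.864.
- 85% of completers qualify, 131 per arm: power 0.848.
- 80% qualify, 124 per arm: power 0.828.
- If the poor attenders are largely the women lost to follow-up anyway, the set stays near 310 and power near 0.90.

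**5. How the ITT analysis relates to the completer set.** A t-test or linear model of one-year percentage reduction needs a one-year value. Every woman who completed that assessment is already in the primary set. As described, ITT can therefore differ from the primary analysis only through its treatment of missing one-year outcomes, which the article does not describe. Under an adherence-based definition, the two would also differ in which attenders they include.

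**The case against.** **Adherence may be high.** The protocol expects no significant adherence problem, and the pilot attendance was 90%. On those figures about 11% of completers (1 − 0.889) would miss the ten-session criterion, so the relevant row in the table is nearer 10% than 30%. This stands as a limit on the likely size. It does not repair the definition.

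**A reader might infer that the ITT analysis uses exactly the same women and must give the same answer.** The documents do not support that. ITT is described as covering everyone randomized, and the remark that "if most participants do not adhere to the assigned intervention or fail to complete the follow-up assessment, the ITT analysis will automatically show no difference" makes sense only if non-completers are counted. Naming the same methods fixes the test and the model, not the handling of missing data. That rule may be in an analysis plan or full protocol that is not shown, so its absence here is not a fault.

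**A reader might infer that the set removes treatment failures.** It removes all women without a one-year assessment. Nothing says that they are failures or that loss differs by arm, so the sign of any bias is open.

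**A reader might infer that nothing governs a disagreement between the two analyses.** The article already ranks them: per-protocol is the main analysis, with an explicit acceptance rule, and ITT is a sensitivity analysis. Requiring success in both is a reasonable preference, not the correction of an error.

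**Co-treatment.** It is tempting also to exclude women who later had incontinence surgery or medication. The follow-up callers do ask ("They also verify if medications have been prescribed, surgery conducted"), but the article places those checks in the calls at three and six months post intervention. Excluding such women could itself remove likely treatment failures.

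**Conclusion.** The concern holds for the definition of the primary set. Data analysis fixes a completer set, calls it per-protocol and credits it with being conservative. It has no adherence condition, contradicts the reason given for choosing it, and makes no use of the ten-of-12 criterion or the attendance records.

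The possible size is material against a 10-point margin: the chance of a false claim roughly doubles, from 0.025 to 0.051, with 10% non-adherers and reaches 0.162 with 30%. This rests on a deficit confined to adherers and on equal non-adherence in the two arms. Attrition adds an uncertainty of either sign, which vanishes if loss and the deficit of lost women are equal across arms. None of this shows that the trial's result will be biased. It shows that the stated rule does not give the protection claimed for it.

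**What to change.** 1. Define the per-protocol set as women who completed the one-year assessment and attended at least ten of the 12 sessions, using the criterion in Interventions and the attendance records described under Adherence.
2. Restate power for that set: about 86% if 89% of completers qualify, about 83 to 85% if 80 to 85% do, and up to about 90% if poor attenders are largely those lost. State the assumption used.
3. Keep the analysis of all one-year completers, label it as such, and drop the description of it as conservative.
4. Run the ITT sensitivity analysis on all randomized women as randomized. Multiply impute missing one-year outcomes from arm, centre, UI type, and the baseline and post-intervention diaries, so that it differs from the completer analysis.

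The cost is revised wording, one imputation program, a smaller primary set and slightly lower stated power. Session attendance and the diaries are already planned data, so no new collection is needed.

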*The ICIQ-Lower Urinary Tract Symptoms quality of life:* a 20-item questionnaire which evaluates quality of life in urinary incontinent patients (0–14 overall score with greater values indicating increasing problems). The ICIQ-LUTSqol provides a detailed and robust measure to assess the impact of urinary incontinence on quality of life with particular reference to social effects [32].

*The geriatric self-efficacy index:* A 20-item instrument that enables measurement of whether a person is confident in their ability to prevent urine loss. It has been shown to be a reliable and valid instrument in the aging female population with UI [35].
*The Broom self-efficacy index (Part A):* A 14-item questionnaire to evaluate women's confidence in performing pelvic floor muscle exercise [36]. The Broom self-efficacy index has solid psychometric properties and is a useful tool to measure self-efficacy in doing PFM exercises [59].
*Patient global impression of improvement PGI-I:* a single-item global index used to measure improvement in urinary continence following PFMT on a 7-point scale that ranges from “very much better” to “very much worse.” The PGI-I has shown acceptable convergent and discriminant validity for measuring outcomes in studies of behavioral treatment for UI [37, 60].
*Satisfaction with treatment:* A single-item tool was used to document and capture perceived satisfaction with treatment: “satisfied” (does not need other treatments); “unsatisfied” (would like another treatment for UI) [17].
*PFM strength, morphometry and function:*
i.
*PFM strength on Oxford scale (digital palpation):* The Oxford scale is a 5-point scale used for PFM strength assessment amongst physiotherapists. Laycock and Jerwood have established intra-therapist reliability of this scale, tested in bent-knee lying [38, 61].ii.
*PFM function:* An intravaginal dynamometric speculum, designed by members of our research team is used to measure passive (tone) and active forces (strength), speed of contraction, coordination with cough and endurance [39]. This instrument has been widely assessed for its psychometric properties including its reliability, validity, and responsiveness [39, 62].iii.

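### The blanket statement that every outcome is continuous is wrong for satisfaction (binary), PGI-I and the Oxford grade (ordinal), and it ties them to unsuitable analysis rules

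*Protocol article*

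**What the plan says.** In the protocol article, Data analysis, the general strategy gives a reason, "Because all primary and secondary outcomes are measured on continuous scales", and draws a rule from it: "the methods outlined below for the analyses of the primary outcome will also apply to all secondary outcomes". It then adds that "the analysis of secondary outcomes will be exploratory in nature".

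The rest of that section sets out the methods so carried over:
- Residuals are checked with Shapiro–Wilk. If normality is clearly violated, a parametric transformation (logarithmic and Box-Cox are the examples) or a non-parametric one is applied.
- The arms are compared by an independent-group t-test.
- Linear model (1) adjusts for centre, UI type and the baseline number of UI episodes. Model (2) adds any variable with an important imbalance.
- Results are reported as adjusted mean differences with 95% CIs.

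The section on pre-treatment covariates makes a further commitment: secondary analyses will also adjust for the pre-treatment value of whichever outcome is being analysed.

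The Secondary outcome measures section defines three measures as follows:
- Satisfaction: "A single-item tool was used to document and capture perceived satisfaction with treatment", with the two answers "satisfied” (does not need other treatments); “unsatisfied” (would like another treatment for UI".
- PGI-I: "a single-item global index used to measure improvement in urinary continence following PFMT on a 7-point scale".
- Digital palpation: "The Oxford scale is a 5-point scale used for PFM strength assessment amongst physiotherapists".

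All three are named in the specific objectives.

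**The concern.** The article's own definitions contradict the reason it gives for its choice of method. This is not detail left to a later analysis plan. The text states a premise, derives a binding rule from it and applies the rule to every secondary outcome. An analysis plan that follows it inherits the error, and one that corrects it departs from the published protocol.

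What is at stake is how the results can be read. Satisfaction and PGI-I are the participants' own verdict on the treatment, which matters in a trial meant to support a change in first-line care. Readers need proportions for the first and a sensible ordinal comparison for the second. If the mismatch is noticed only at analysis, the method will be chosen after the data are in.

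**Working it through.** **1. The plan's own figure, to see whether it is touched.** Inputs from the Sample size calculation section: margin 10, SD 27, true difference 0, one-sided α 0.025, power 90%.

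n per arm = 2 × (1.960 + 1.282)² × 27² / 10² ≈ 153.2, so 154 by the normal approximation. With the noncentral t distribution, power is 0.8997 at 154 and 0.9015 at 155, so the stated 155 per arm (310 in total) is reproduced. For attrition, 364 × 0.85 = 309.4, in line with the stated 364. All of this concerns the percentage reduction in UI episodes. No secondary outcome enters it.

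**2. Stated premise against defined scales.**

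| Measure | Scale as defined | Continuous? |
|---|---|---|
| Satisfaction | two categories | no, on any reading |
| PGI-I | one item, 7 ordered categories | no, ordinal |
| Oxford scale | 5-point palpation grade | no, ordinal |

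Summed questionnaire scores, pad weight, dynamometry and ultrasound measures can reasonably be treated as continuous.

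**3. Is another between-arm method given for these three?** No. Frequency distributions for categorical and binary variables belong to the preliminary descriptive step. The logistic model in the section on predicting response is for a reduction of at least 50% in UI episodes, not for satisfaction, PGI-I or Oxford grade.

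**4. What the normality rule does to satisfaction.** In a simulation with 155 women per arm (300 runs per setting, assumed satisfaction rates of 50%, 70% and 90%), Shapiro–Wilk on the residuals rejected normality in 100% of runs, both on the raw 0/1 values and after log(y + 1). The reason is structural: any transformation of a two-valued variable is still two-valued or, if it maps both values to one, constant.

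Let RD be the difference between arms in the proportion satisfied.
- Untransformed 0/1 coding: mean difference = RD.
- log(y + 1): the values become 0 and log 2 = 0.693, so mean difference = 0.693 × RD.
- Ranks with ties averaged, with n₀ zeros and n₁ ones: the gap between the two ranks is [n₀ + (n₁ + 1)/2] − (n₀ + 1)/2 = (n₀ + n₁)/2. With 310 analysed, mean difference = 155 × RD.

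Each transformation only rescales the comparison. The t statistic and p-value do not change, normality is not achieved, and the estimate is no longer a difference in proportions.

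**5. The ordinal items.** For one assumed 7-category distribution (30, 35, 20, 10, 3, 1 and 1%) and one assumed 5-category distribution (5, 20, 35, 30 and 10%), Shapiro–Wilk again rejected in 100% of runs, raw and after log. In these examples the parametric route does not reach its aim either. A rank-based route could still serve.

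**6. Baseline adjustment.** PGI-I measures improvement following training, and satisfaction concerns the treatment received. Neither can have a pre-treatment value, so the own-baseline commitment in the section on pre-treatment covariates cannot be met for them. Model (1) in Data analysis is different: it uses the baseline number of UI episodes, which every woman has, so it can be fitted to both. The Oxford grade can have a baseline, because Trial design lists physical and gynecological exams at the pre-intervention evaluation.

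**The case against.** The best defence has four parts.

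*The analysis of satisfaction is not invalid.* The mean of a 0/1 variable is a proportion, so an untransformed mean difference is a risk difference and a linear model gives an adjusted one. At about 155 per arm the t-based interval is close to the usual large-sample interval unless the proportions are extreme. This stands. A reader might infer that the satisfaction result would be meaningless or the test wrong, and the documents do not support that. What is lost is readability, and it is lost because the plan's rule calls for a transformation that cannot succeed.

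*The plan allows a non-parametric transformation.* If that means ranks (an assumption, since the cited source is not at hand), a t-test on ranks is close to a Wilcoxon test, which is acceptable for PGI-I and Oxford grade. Comparing means of 5- and 7-point grades is also common and often tolerable at this size. This stands too, and a preference for proportional odds over ranks is partly taste. It does not help satisfaction, and it does not make the premise true.

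*Model (1) works for every outcome.* Correct. A reader might infer that it cannot be fitted to PGI-I or satisfaction, but it asks only for baseline UI episodes. The adjustment that cannot be made is the one in the section on pre-treatment covariates.

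*The outcomes are exploratory.* Also correct, and pelvic floor strength is measured by dynamometry as well, so it does not rest on the Oxford grade alone. This limits the weight of the point but does not remove the contradiction.

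**Conclusion.** The point holds in a limited form. The statement that all outcomes are continuous contradicts the article's own definitions of three secondary measures. It is plainly wrong for satisfaction and inexact for PGI-I and Oxford grade. For satisfaction the prescribed check and transformation are futile and turn a risk difference into a less readable coefficient. For satisfaction and PGI-I the own-baseline adjustment is impossible.

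It would go too far to infer that the non-inferiority conclusion is at risk. The margin, the decision rule and the 155 per arm all rest on the percentage reduction in UI episodes, and the affected outcomes are declared exploratory.

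That no transformation can make a two-valued item normal needs no assumption. The rejection rates rest on the assumed satisfaction rates and category distributions given above. The absence of a pre-treatment value is read from what the two items measure. The correction is worth making before analysis, as a matter of sound specification rather than rescue of the trial.

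**What to change.** - **Data analysis, general strategy:** limit the sentence, and the carry-over of primary-outcome methods, to outcomes measured on continuous scales.
- **Data analysis, normality check:** limit the Shapiro–Wilk and transformation rule to the same outcomes.
- **Satisfaction:** report the proportion satisfied in each arm with a risk difference and/or odds ratio and 95% CI, for example from logistic regression adjusted for centre, UI type and baseline UI episodes.
- **PGI-I and Oxford grade:** name one ordinal or rank-based method in advance, with Oxford grade also adjusted for its own baseline.
- **Pre-treatment covariates:** exempt satisfaction and PGI-I from adjustment for their own pre-treatment value. Model (1) can stay as it is for them.

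The cost is a few sentences and standard procedures. The team already plans a logistic model for another endpoint. No new data are needed, and neither the sample size nor the primary analysis changes.
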